## 2. Methods

### 2.1. Study Design

In accordance with the Consolidated Standards of Reporting Trials statement (CONSORT) [27,28], a pilot, cluster-randomized controlled trial (RCT) will be conducted. Due to the nature of the intervention, a double-blind study design is not possible given that participants will be aware of their group designation, and as such, a single-blind design will be adopted (all assessments will be conducted by research staff who remain unaware of group assignment). This study received ethical approval from the University of Western Ontario’s Research Ethics Board (REB# 111890) and is registered with the Clinical Trials Registry provided by the US National Library of Medicine (NCT03695523; https://clinicaltrials.gov/).

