### 2.6. Development and Implementation of the Childcare PLAY Policy

To promote policy engagement, buy-in, and suitability, the policy was developed by our research team in collaboration with an advisory committee that included childcare organizations and centre administrators, childcare providers, municipal childcare stakeholders, and a policy expert. The policy was created following a review of relevant literature on the importance of outdoor play [32], unstructured activity [29,33], and informed by the Canadian 24-Hour Movement Guidelines for the Early Years (0–4 years; [3]). The current version of the policy includes eight statements that are designed to provide specific recommendations for time in energetic play (i.e., minimum of 40 min/day), outdoor time (i.e., 120 min/day), and suggests short (i.e., 15–30 min), frequent (i.e., 3–4 times/day) outdoor periods during childcare hours. It requires that children be exposed to a variety of indoor and outdoor physical activities to promote physical literacy and recommends appropriate role modelling of screen-based technology, with no screen time permitted for children during childcare hours. Sustained sedentary time is recommended to be disrupted and replaced with physical activity. See Appendix A for the Childcare PLAY policy.

Experimental Condition. For eight weeks, childcare providers in the experimental centres will be asked to implement the written policy that outlines optimal physical activity daily affordances and sedentary time recommendations during childcare. Prior to the eight-week intervention period, childcare providers will participate in a training session, led by the project coordinator. The session will last approximately an hour in length, which will detail the characteristics of the study design, review the policy, its implementation, and study tools (e.g., accelerometer logs).

Control Condition. Childcare centres randomly assigned to the control group will be asked to continue their typical daily curriculum for the duration of the eight-week intervention and follow-up period. Upon completion of the study, all centres allocated to this group may opt to receive a copy of the written physical activity policy and the training regarding its implementation.

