### 2.7. Measures

A variety of tools will be used to assess the feasibility and effectiveness of the Childcare PLAY Policy (Table 2).

Demographic Information (Parents and Childcare Providers). Parents of participants will be asked to complete a demographic questionnaire at baseline to describe participants and their families (e.g., children’s age, sex, ethnicity, family income, parental education), as well as the children’s physical activity participation outside of childcare (e.g., organized sport or activities). Parental/guardian weekly engagement in MVPA and their view of themselves as a physical activity role model will be measured. Childcare providers and directors will complete a demographic questionnaire at baseline to capture information related to their age, sex, employment status, years of childcare experience, and level of education. Childcare providers will also report time in MVPA and their view of themselves as physical activity role models. No personal identifiers will be stored with participant data.

Physical Activity (Children). Toddlers’ and preschoolers’ physical activity will be measured using ActiGraph™ (ActiGraph, LLC, Pensacola, Florida) accelerometers—the gold standard for measuring young children’s sporadic physical activity patterns in field settings [34,35,36]—for five consecutive days, during childcare hours only. This process will be undertaken pre-intervention (week 0), mid-intervention (week 4), post-intervention (week 9), and at six-month follow-up. Raw data will be collected to capture the sporadic activity and intermittent periods of rest of the young participants. The accelerometers will be worn on the right hip (above the iliac crest) and will begin collecting activity data on the morning of the first day of data collection. Wear-time of the accelerometers (i.e., the time when it is fitted and removed from each child) will be recorded for each participating child by childcare providers using a daily log. Validated and age appropriate cut-points will be applied to the data to delineate the different activity intensities [37].

Anthropometric Measures (Children). Height (using a Seca 214 “Road Rod” Portable Stadiometer; nearest 0.1 cm), weight (using a Tanita 700-TBF300GS Body Fat Analyzer w/Goal Setter scale; nearest 0.1 kg), and waist circumference (using a measuring tape; nearest 0.1 cm) will be assessed at baseline. The data collected will be used to calculate the child’s standardized body mass index score (BMI-z).

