Childcare Environment (Childcare Providers and Directors). The validated Environment and Policy Assessment and Observation—Self-Report (EPAO-SR; [39]) instrument examines the classroom physical environment and physical activity practices in childcare centres; this tool consists of two subscales, Space, Equipment, and Environment (eight items) and Practices around Physical Activity (three items). We will adapt the tool to conform with the Canadian context and remove the nutrition content (as seen in Ott et al.’s paper) [22]. This tool will be administered to childcare providers once during each week of data collection. The information solicited from this questionnaire will provide useful context to help better understand each classroom’s physical activity environment and practices and whether these change after the policy is implemented. The EPAO-SR Today [39], which entails six subscales (Morning Outdoor Activities (seven items); Morning Indoor Activities (eight items); Nap/Rest Time (three items); Afternoon Outdoor Activities (seven items); Afternoon Indoor Activities (three items); and Other Activities (three items)) will also be completed by one childcare provider per classroom on one chosen day at each data collection time point. This validated tool provides a snapshot of the specific activities in which the children engaged during morning and afternoon indoor and outdoor periods. Finally, the validated Director General EPAO-SR [39], which consists of two subscales (Childcare Environment (six items) and Physical Activity Policies (11 items)) also adapted for use in Canada without the nutrition subscale, will be administered to all centre directors at baseline. This will assess the presence of any existing physical environment characteristics that may inhibit or promote physical activity, and existing policies related to physical activity and sedentary time that may exclude a centre from participating in the study.

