## Appendix A. Childcare PLAY Policy

Childcare programs encourage all children to engage in physical activity frequently throughout the day, with a focus on outdoor energetic free play and deliberate interruption of sustained periods of sedentary behaviour.

Directed by the Canadian 24-Hour Movement Guidelines for the Early Years (0–4 years)*, childcare programs are expected to:

1. Encourage children to engage in higher intensity energetic play (i.e., activities that induce sweating and heavy breathing) often throughout the day with a goal of accumulating a minimum of 40 min each day. More is better.
2. Expose children to a variety of indoor and outdoor physical activities, including both child-directed and teacher-facilitated active play daily.
3. Outdoor time is offered for a minimum of 120 min each day, unless extreme weather (i.e., heat or cold alert) prevents it. When extreme weather occurs, the opportunity exists for children to engage in active play indoors.
4. Short, frequent outdoor sessions are most conducive to higher intensity physical activity among children; therefore, short bouts (e.g., 15–30 min) of outdoor time are recommended often (e.g., 3–4 times a day).
5. Unstructured (i.e., child-directed) free play is predominant during outdoor time. When activity levels decline, childcare practitioners encourage continued energetic play through structured activity, participation alongside children, and use of verbal prompts.
6. Encourage children to develop physical literacy by practicing fundamental movement skills often throughout the day (e.g., running, skipping, hopping, or jumping).
7. The appropriate use of screen-based technology is role modelled by childcare practitioners by avoiding it when children are present. Screen-based technology is not offered to children under 2 and is not recommended during childcare hours.
8. Programming is designed to break up sustained sedentary time using indoor movement-based activities.

* These guidelines recommend that children over 1 year of age engage in 180 min of physical activity at any intensity each day, and by age 3, at least 60 min of this time is spent in higher intensity physical activity, known as energetic or active play.

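### The day for the EPAO-SR Today form is left to choice rather than fixed in advance, so the plan permits day selection that differs by arm

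*Protocol article*

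**What the plan says.** Section 2.7 (Childcare Environment) says that the EPAO-SR Today "will also be completed by one childcare provider per classroom on one chosen day at each data collection time point". Its purpose is described as follows: "This validated tool provides a snapshot of the specific activities in which the children engaged during morning and afternoon indoor and outdoor periods". Section 2.8 makes it one of three surveys behind 13 best-practice scores, and change in practices and environment is explored by logistic regression on group and time. The environment outcome is a secondary objective.

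On blinding, section 2.1 states that "a double-blind study design is not possible given that participants will be aware of their group designation", yet it also says that "all assessments will be conducted by research staff who remain unaware of group assignment". Section 2.6 adds, for the experimental centres: "Prior to the eight-week intervention period, childcare providers will participate in a training session, led by the project coordinator". That session covers both the policy and the study tools.

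On weather, statement 3 of Appendix A reads: "Outdoor time is offered for a minimum of 120 min each day, unless extreme weather (i.e., heat or cold alert) prevents it".

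Other measures have set days. Accelerometers are worn "for five consecutive days, during childcare hours only", and the policy adherence log is kept on Mondays, Wednesdays and Fridays.

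**The concern.** A one-day form is only as representative as the day it describes. Here the sampling rule is a choice, with no stated chooser, no rule, and no requirement that the day be fixed before the wave or picked in the same way in both arms. The reporter knows the arm and, in experimental centres, has been taught the energetic-play and outdoor-time targets. If experimental classrooms tended to report a better day than control classrooms did, the between-group comparison of Today-based scores would show change that did not occur. Outdoor content varies with the weather, so choosing the day can also mean choosing the weather.

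The blinding statement in 2.1 offers no protection, because a form filled in by the provider is not an assessment by blinded staff. The trial is a pilot meant to precede a larger evaluation, so a weak measurement procedure could be carried forward.

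**Working it through.** The plan gives no figure for this outcome, so there is none to reproduce. The sample size of 99, 175 and then 218 children concerns children's activity and is not an input.

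**How much of the outcome is exposed.** From the item counts in 2.7:
- Today: 7 + 8 + 3 + 7 + 3 + 3 = 31 items, of which 7 + 7 = 14 are outdoor items.
- General form, also repeated at each wave: 8 + 3 = 11 items, with no chosen activity day described.
- Director form: 6 + 11 = 17 items, at baseline only, so it cannot show change.

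Today thus supplies 31 of 31 + 11 = 42 repeated items (74%). Item counts are not score weights, but Today is not a marginal input.

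**Possible size of the bias.** The following are assumptions, not document figures. A yes/no practice is met on a share p of days in both arms (no true effect). Days are independent. The choice is among k = 5 days, borrowed from the accelerometer week. A share q of experimental classrooms reports its best day, and no control classroom does.

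Reported rate in the experimental arm = (1 − q)·p + q·[1 − (1 − p)^k]. The control rate is p. Spurious difference = q·[1 − (1 − p)^k − p].

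| p | best of five: 1 − (1 − p)^5 | q = 0 | q = 25% | q = 50% | q = 100% |
|---|---|---|---|---|---|
| 20% | 1 − 0.8^5 = 67% | 0 | 12 points | 24 points | 47 points |
| 30% | 1 − 0.7^5 = 83% | 0 | 13 points | 27 points | 53 points |
| 50% | 1 − 0.5^5 = 97% | 0 | 12 points | 23 points | 47 points |

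With the better of only two days and p = 50%, the reported rate under full selection is 1 − 0.5^2 = 75%, a difference of 25 points. With q = 25% that is 0.25 × 25 = 6 points.

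If control classrooms also select, q is replaced by the difference in selecting shares between arms, and the bias vanishes when the shares are equal. It also vanishes if study staff set the day without regard to arm.

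On a continuous score, simulation puts the expected gain from taking the best of 2, 3, 4 or 5 independent days at 0.57, 0.85, 1.03 or 1.16 day-to-day standard deviations.

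**The case against.** A reader might infer that experimental providers pick a good day and that the environment result is therefore biased. The article does not support that.

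- **Who chooses.** The sentence is passive. The provider completes the form, but the chooser is not named. Study staff could set the day, and a journal article may leave that to the full protocol. This stands as a limit on the claim: selection is possible, not shown. It does not remove the point, because the article does state a sampling rule, and that rule is a choice, whereas it sets days for the log and the accelerometers.
- **Other daily records.** Today is not the only one. The adherence log covers each policy statement on fixed days, with weather among the reasons for non-adherence, and it overlaps the week 4 form. This stands, although the log does not run at baseline, week 9 or six months.
- **Waves.** Only week 4 falls while the policy is in force, and the article does not say whether providers know their arm at baseline. The motive to report a policy-compliant day is therefore weaker outside week 4.
- **Weather.** Unselected weather is mostly noise shared by both arms. It biases the comparison only if days are selected, or scheduled, differently by arm.
- **Accelerometry.** One might fear that the form describes a day without activity data. It is collected in the same four waves, so this is speculative.
- **Size.** The large figures assume that every experimental classroom and no control classroom selects. Weather on neighbouring days may not be independent, and a form filled in on the day does not let a provider compare all five days first. Both considerations pull towards smaller values.
- **Scope.** Today is one of three surveys, in a secondary and exploratory analysis of a pilot.

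**Conclusion.** The narrower point holds. The article sets one chosen day per wave for a one-day self-report by a provider who knows the arm, and neither names the chooser nor fixes the day in advance. This leaves room for selection that differs by arm in the Today-based part of the environment outcome. It does not show that such selection will occur, and it does not touch the children's activity outcomes or the General form's timing.

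The bias starts at zero. At p = 50% its ceiling is 47 points under complete one-sided selection among five independent days; a quarter of experimental classrooms selecting gives about 12 points. These figures rest wholly on the stated assumptions and move somewhat with p. The point is a cheap improvement to a secondary measure, not a threat to the trial's main conclusions.

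Separately, the statement in 2.1 that blinded staff conduct all assessments cannot describe provider-completed forms.

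**What to change.** In 2.7, replace the chosen day with a day that research staff set for each classroom before each wave, by one rule in both arms. One workable rule is a randomly drawn weekday within the five-day accelerometer week. Allow a substitute day only for closure or provider absence, with the reason noted, and record the weather on the day reported.

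In 2.1, restrict the blinding statement to the assessments that staff actually perform, and identify the provider-completed forms as unblinded self-report.

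The cost is a few lines of wording, a pre-drawn list of days and slightly less scheduling freedom for centres. The change removes day selection as a source of bias. It does not remove reporting bias from knowing the arm, and a classroom told its day ahead of time could still prepare for it.

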### 2.8. Analysis

All data will be entered, verified, and stored in our lab. Baseline characteristics of the children and the childcare centres will be summarized descriptively; participant characteristics for those who complete the study and those who drop out will be explored. All statistical analyses will be performed in R [31], using the lme4 [40] and lmerTest packages [41].

Implementation Log. Frequencies and percentage scores will be calculated to reflect adherence to policy statements and reasons that compliance was not attained will be reported descriptively.

Program Evaluation Survey and Interviews. Means and standard deviations of survey item ratings will be provided. Responses to open-ended program evaluation survey and interview questions will be analyzed using thematic content analysis [42] using QSR NVivo.

Physical Activity. Children’s physical activity data will be analyzed using a series of linear mixed effects models for each of the three outcome variables (i.e., TPA, MVPA, and sedentary time). Group (experimental versus control) and time (baseline, mid-intervention, post-intervention, and six-months post-intervention) will be modelled as a fixed effect, and will be evaluated using *t*-tests, with a Satterthwaite approximation determining degrees of freedom. Descriptive survey data will be analyzed using frequencies, *t*-tests, and chi-square tests.

Childcare Providers’ Self-Efficacy. Descriptive statistics will be reported to indicate changes in childcare providers’ self-efficacy specific to implementing physical activity in childcare. Classical test theory will be used to assess internal consistency of the scales, exploratory factor analysis will be used to assess the factorial validity of the measured constructs, and item response theory will be used to explore the item and scale characteristics of the measurements used to assess the two polytomous constructs in this study (i.e., task and barrier self-efficacy). Factor analysis and classical test theory analyses will be undertaken within the psych package [43] and the ltm package [44] will be used for the item response theory analyses.

Childcare Environment. The EPAO-SR is structured around 13 best-practices scores which are obtained from the three surveys [39]. The revised EPAO-SR tools will be scored, in line with the scoring protocols as described by the tool creators [39], to generate a score for each of the 13 best practices. Descriptive statistics will be used to describe classroom practices and changes in classroom practices and environment will be explored using 2 × 5 logistic regression models (two groups, five time points).

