### Hypothesis

It is hypothesized that the physical activity and sedentary time policy will be viewed as feasible to implement. Additionally, it is anticipated that young children who attend a centre implementing the physical activity policy (i.e., experimental group) will display increased rates of TPA, MVPA, and reduced sedentary time from baseline to post-intervention, with no change observed for children at centres assigned to the control group. While activity levels are expected to decrease at follow-up, when providers are asked to stop enforcing the policy, it is believed that activity levels at this time point will still be higher than those recorded at baseline. For childcare providers from the experimental group, we expect an increase in self-efficacy implementing physical activity in childcare after adopting the policy and expect additional supportive changes in the childcare environment as a result of the policy implementation.

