### 2.3. Sample Size

To secure a representative sample of children in childcare, a random cluster sampling strategy will be used. In a meta-analysis exploring the effectiveness of 15 physical activity interventions targeting preschool-age children, Gordon and colleagues [29] reported that most studies had a small-to-moderate effect (Hedges *g* = 0.4) for change in young children’s total physical activity levels after participating in an intervention. If we convert this to f2, we can estimate this effect size to be approximately 0.12. Using the pwr package [30] within R version 3.6.0 [31], a minimum sample size of 99 children will be required (assuming 80% power and an experiment-wise alpha of 0.05). To account for a clustering effect, using an intra-cluster coefficient of 0.05, and an average cluster size of 16 children, the design effect is: 1 + 0.05 (16 − 1) = 1.75. Therefore, the sample size will be inflated to 175. Based on our recently conducted studies using accelerometry within the childcare environment [9], an anticipated loss to follow-up/accelerometer non-compliance rate of 20% is anticipated. To adjust for this, we aim to recruit 218 children.

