## 3. Discussion

Evidence-informed approaches to supporting and encouraging appropriate physical activity participation (and limiting periods of sedentary time) during childcare hours are warranted. A substantial body of evidence suggests that childcare programming and the environment strongly influence young children’s physical activity levels [45,46]. In fact, childcare centres influence preschoolers’ activity levels more than individual-level factors, such as age, sex, and ethnicity [47]. Despite recognition that childcare venues are an ideal setting to intervene and the call for institutional-level physical activity policies in childcare centres [23], the feasibility and effectiveness of a physical activity and sedentary time policy, specifically within the Canadian context, is lacking. A written physical activity and sedentary time policy may help to promote providers’ self-efficacy by providing specific direction in terms of how to best engage children in daily activity. Moreover, creating and implementing such policies would ensure that all children attending these facilities are afforded the opportunity to be physically active, and offer a greater chance of meeting the daily recommendation. Young children spend two-thirds of their day in childcare, suggesting that two-thirds of the daily movement requirement (180 mins of TPA; 60 mins of MVPA), may be achieved during childcare hours (120 mins of TPA; 40 mins of MVPA). Implementation of an activity-focused childcare policy provides an opportunity to “level the playing field” in terms of ensuring consistent affordances within this setting and represents a promising population-based approach (with access to over 50% of this Canadian cohort) for supporting active behaviours.

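### Week-0 activity is modelled as one of four outcome occasions with no stated baseline adjustment or common week-0 mean, so baseline data already collected are used less efficiently than they could be

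*Protocol article*

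**What the plan says.** Section 2.7 (Measures) schedules accelerometry in both arms: "This process will be undertaken pre-intervention (week 0), mid-intervention (week 4), post-intervention (week 9), and at six-month follow-up". Table 2 confirms it. A pre-policy value of all three activity outcomes is therefore collected for each child with valid wear.

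Section 2.8 (Analysis) says the activity data will be "analyzed using a series of linear mixed effects models for each of the three outcome variables". Group is a fixed effect, and "time (baseline, mid-intervention, post-intervention, and six-months post-intervention) will be modelled as a fixed effect". Tests are t-tests "with a Satterthwaite approximation determining degrees of freedom". The text states no baseline covariate, no equality of the arms at week 0, no group-by-time term and no random-effects structure.

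The Hypothesis section words the expected effect as change: in the experimental arm, more activity and "reduced sedentary time from baseline to post-intervention, with no change observed for children at centres assigned to the control group". Section 2.3 likewise takes its effect size, Hedges g = 0.4, for change in total physical activity.

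The Discussion remarks that "childcare centres influence preschoolers’ activity levels more than individual-level factors, such as age, sex, and ethnicity".

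**The concern.** With four centres per arm, precision on the activity outcomes is scarce. If the centre matters as much as the Discussion says, the arms may well differ at week 0 by chance.

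The wording in section 2.8 can be read in two ways, and each loses something.

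- **Group-by-time contrast with free week-0 means.** This fits the change hypothesis. It subtracts the whole baseline difference, noise included, instead of the part that predicts follow-up.
- **Group main effect only.** This is the literal wording. The coefficient averages over week 0, when no policy is in force, and so understates the effect.

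At stake is the width of the intervals for TPA, MVPA and sedentary time. No extra data are needed to narrow them.

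**Working it through.** **Inputs from section 2.3.** 99 children, ICC 0.05, cluster size 16, design effect 1 + 0.05 x 15 = 1.75, 175 children after inflation, 20% loss, target 218, g = 0.4, two-sided 0.05. The chain reproduces to rounding: 99 x 1.75 = 173.25 (stated 175, which is 100 x 1.75), and 175/0.8 = 218.75 (stated 218). The effective size is 175/1.75 = 100.

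**Assumption.** The correlation rho between a child's week-0 and follow-up activity is not given. I use 0.3 to 0.8.

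**Relative variance k of the arm difference at one follow-up (outcome SD 1, compound symmetry)**
- Follow-up only: k = 1
- Change, free week-0 means: k = 2(1 - rho)
- Baseline conditioned on, or common week-0 mean: k = 1 - rho^2

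The ratio of the last two is (1 + rho)/2, which is below 1 for every rho below 1. The direction therefore does not depend on the assumed value.

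**Individual-level power.** Noncentral t, 98 df, ncp = 0.4 x sqrt(100)/(2 sqrt(k)) = 2/sqrt(k). Follow-up only gives 50.8% throughout.

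| rho | change | conditioned | gain (points) |
|---|---|---|---|
| 0.3 | 38.7% | 54.6% | 16 |
| 0.5 | 50.8% | 62.8% | 12 |
| 0.6 | 60.0% | 69.7% | 10 |
| 0.7 | 72.5% | 79.2% | 7 |
| 0.8 | 87.9% | 91.0% | 3 |

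These powers use g = 0.4 directly. They do not use the f2 of 0.12 behind the plan's 80%, so only the differences matter here.

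**Centre-level power.** 4 v 4 centres, 175/8, or about 22 children each, ICC 0.05, t with 6 df. Let p be the correlation of a centre's effect between week 0 and follow-up (its persistence), with rho now within centre.
- Variance of a centre mean: V = 0.05 + 0.95/22 = 0.0932
- Correlation of centre means: R = (0.05p + 0.0432 rho)/0.0932
- ncp = 0.4/sqrt(Vk/2), with k = 2(1 - R) for change and 1 - R^2 for a common week-0 mean

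At rho = 0.5, follow-up only gives 34.5%.

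| p | R | change | common week-0 mean | gain (points) |
|---|---|---|---|---|
| 0.5 | 0.500 | 34.5% | 43.6% | 9 |
| 0.8 | 0.661 | 47.2% | 54.4% | 7 |
| 1.0 | 0.768 | 62.4% | 67.7% | 5 |

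Over rho 0.3 to 0.8 and p 0.5 to 1.0, the gain runs from 10 points (rho 0.3, p 0.5: 30.0% to 40.0%) to 1 point (rho 0.8, p 1.0: 94.5% to 95.3%). The variances are treated as known, so these gains are somewhat optimistic.

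**A child-level covariate alone.** With one slope b close to the within-centre value 0.5, k = 1 + b^2 - 2bR. At p = 1.0 this is 1.25 - 0.768 = 0.482, against 2(1 - 0.768) = 0.464 for change. Power is about 61% against 62%, so there is no gain.

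**Main effect only.** With no effect at week 0 and a constant effect D at the three later occasions, the group coefficient estimates (0 + D + D + D)/4 = 3D/4.

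**The case against.** **The article may simply be condensed.** Parameterisation is often left to a fuller plan, and listing baseline as a level of time is also how a common-baseline model is coded. This stands in part. The quoted sentence does not exclude the remedy, and if a fuller plan already constrains the week-0 means, nothing is lost. But the article does fix week 0 as a response occasion and states no adjustment, so the point can be raised on its wording.

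**The model answers the stated question.** The hypothesis and the effect size both concern change. This also stands: over repeated randomisation the change contrast is unbiased, so the issue is efficiency and the handling of chance imbalance.

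Three stronger readings are tempting, and the documents do not support them.
- *That the baseline does nothing for precision.* It enters through the within-child correlation. In the individual-level calculation the change contrast beats follow-up only (50.8%) once rho exceeds 0.5, reaching 60.0%, 72.5% and 87.9% at rho 0.6, 0.7 and 0.8.
- *That the loss is 12 power points.* That figure belongs to an individual-level test at an assumed rho of 0.5. With eight centres at the same rho it is 9, 7 or 5, and strongly persistent centre differences push it to the low end.
- *That allocation was unstratified.* Section 2.4 says only that centres are randomly allocated, four to each arm. The absence of stratification would be read from silence.

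**Conclusion.** The point holds as one of efficiency. As worded, section 2.8 does not secure the full value of the week-0 measurements. Conditioning on baseline is more precise than a free-baseline change contrast for any rho below 1. The realistic size is about 1 to 10 power points at centre level, or 3 to 16 in the simpler individual-level calculation. Both rest on assumed correlations, compound symmetry and g = 0.4. The dilution to 3/4 applies only if the group main effect alone is tested and the effect is constant after week 0. The Hypothesis section expects some decline at follow-up, so that fraction is illustrative.

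The planned model is not invalid. Activity outcomes are secondary in a pilot whose primary aim is feasibility, although section 2.3 sizes the trial on total physical activity. The change is worth making because it costs almost nothing.

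**What to change.** In section 2.8, for TPA, MVPA and sedentary time alike:

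- Keep all four occasions in the response, and constrain the two arms to a common week-0 mean.
- Name the group-by-time terms at week 4, week 9 and six months as the effects to be tested.
- State random effects for centre (including centre-by-time) and for child.

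An alternative is to model only the three follow-ups, with both the child's own week-0 value and the centre-mean week-0 value as covariates. The child's value alone is not enough, because it can gain nothing when centre differences persist.

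This changes analysis wording only, with no new data or procedures. The constrained model relies on week-0 measurement being unaffected by allocation. The covariate version drops children without valid week-0 wear and spends a centre-level degree of freedom. At rho 0.5, repeating the centre-level calculation with 5 df in place of 6 gives about 41%, 51% and 64% for p of 0.5, 0.8 and 1.0, so part of its gain is given back. The constrained model is the better first choice.
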